## Abstract

**Introduction:**

Antibiotic overuse is prevalent in neonatal intensive care units (NICUs) and is associated with adverse neonatal outcomes and antimicrobial resistance. While antimicrobial stewardship programs (ASPs) have been implemented globally, antibiotic utilization rates remain high in China, particularly in resource-limited regional settings. Evidence indicates that guideline dissemination alone is insufficient to alter established prescribing behaviors, underscoring the need for pragmatic, system-level quality improvement (QI) strategies. This study outlines a multicenter QI initiative designed to optimize antibiotic use in NICUs within a resource-limited region of China.

**Methods:**

This ongoing study uses a multicenter, before-and-after interrupted time series (ITS) design across five NICUs in the Suqian region. A bundled ASP intervention is being implemented, comprising standardized early-onset sepsis risk stratification, mandatory 48–72-h antibiotic reassessment, protocolized empirical antibiotic regimens, and a two-tier governance structure supported by monthly Plan–Do–Study–Act cycles. Monthly aggregated data are collected during a 12-month baseline period (2025) and a 12-month intervention period (2026–2027). Primary outcomes are the antibiotic use rate and the antibiotic utilization rate (days of therapy per 1,000 patient-days). Balancing measures include the incidence of late-onset sepsis, in-hospital mortality, and antibiotic re-initiation rate. Process adherence is monitored as a key implementation indicator. Segmented regression ITS analysis and statistical process control charts are used to evaluate the intervention effect.

**Discussion:**

This study evaluates a pragmatic, workflow-integrated ASP QI model for regional NICUs with limited resources. By integrating standardized clinical pathways, structured reassessment, and continuous data-driven feedback within a multicenter collaborative framework, the intervention aims to safely reduce unnecessary antibiotic exposure. The findings will provide evidence to inform scalable antimicrobial stewardship strategies in similar resource-constrained neonatal care settings.

**Clinical trial registration:**

https://www.chictr.org.cn/, dentifier: ChiCTR2600120301.

## Introduction

1

Antibiotics are among the most frequently prescribed medications in neonatal intensive care units (NICUs) (1). However, substantial evidence consistently indicates widespread overuse of antibiotics in NICU clinical practice (2, 3). Unnecessary antibiotic exposure is increasingly linked to adverse neonatal outcomes, including necrotizing enterocolitis (NEC), late-onset sepsis (LOS), and multidrug-resistant organisms (4–8). Consequently, optimizing antibiotic use in NICUs has become an important global public health priority to improve neonatal outcomes (9).

Despite the gradual implementation of antimicrobial stewardship programs (ASPs) worldwide, marked variations in antibiotic use persist across countries and regions, with particularly high levels reported in China (10). In some high-income countries, antibiotic utilization rates (AURs) in NICUs have declined to approximately 250 days of therapy (DOTs) per 1,000 patient-days (11). In contrast, recent multicenter surveys in China have reported median NICU AURs of 500–530 DOTs per 1,000 patient-days in regions such as Hunan and Jiangsu provinces, substantially exceeding levels reported in many high-income settings (12–14). The Suqian region, located in northern Jiangsu Province, has relatively limited healthcare resources and subspecialty development compared with more developed urban centers within the province. Our baseline assessment demonstrated an AUR of 636 DOTs per 1,000 patient-days in NICUs in the Suqian region in 2024, indicating a particularly high burden of antibiotic use. Therefore, conducting an antimicrobial stewardship intervention in this region holds significant implications for exploring rational antibiotic use pathways in NICUs within resource-limited settings.

Previous studies have shown that the dissemination of clinical guidelines alone or passive educational interventions is often insufficient to change long-established prescribing behaviors among physicians (15). Increasing evidence suggests that systematic quality improvement (QI) strategies are required to achieve sustained practice change (16). Systematic reviews and meta-analyses have demonstrated that QI-based interventions can effectively reduce antibiotic use in NICUs without increasing neonatal mortality or other serious adverse outcomes, supporting the safety and potential benefits of such approaches (17). Nevertheless, directly transferring well-established QI models from other institutions to regional or resource-limited hospital systems remains challenging. Barriers include constrained staffing resources, differences in safety culture (such as defensive medical practices), and locally specific antimicrobial resistance epidemiology (18, 19). Accordingly, there is a clear need to develop QI strategies that are pragmatic, sustainable, and readily integrated into routine clinical workflows within local practice contexts, thereby narrowing the gap between guideline recommendations and real-world clinical practice.

Against this background, the present study aims to evaluate the effectiveness of a regional, multicenter QI program in reducing antibiotic use in NICUs. Using a before-and-after interrupted time series (ITS) design, this study will implement a bundled intervention across five NICUs in the Suqian region, incorporating infection risk stratification, mandatory 48-h antibiotic reassessment, and a two-tier governance structure. The impact of this intervention on antibiotic utilization and associated clinical outcomes will be systematically assessed.

## Methods

2

### Study design

2.1

This multicenter QI initiative utilizes a before-and-after ITS design to evaluate changes in antibiotic use and clinical outcomes in Suqian NICUs. Positioned as a practice-oriented initiative, it focuses on assessing the clinical effectiveness of integrating interventions into routine workflows rather than implementation mechanisms.

The design, implementation, and reporting of this study follow the Standards for Quality Improvement Reporting Excellence (SQUIRE) 2.0 guidelines (20). The study protocol was approved by the Ethics Committee of the Suqian Municipal Science and Technology Bureau (approval number: 2025-SR-0023). As this project constitutes a system-level QI initiative aimed at process optimization, a waiver of informed consent was granted by the ethics committee. All patient data are de-identified to ensure confidentiality. The study has been registered with the Chinese Clinical Trial Registry (registration number: ChiCTR2600120301).

### Study Period

2.2

The study comprises three consecutive phases:

**1) Baseline period (January 2025 to December 2025):**

During the baseline period, all participating centers followed their usual clinical practices for the diagnosis and management of neonatal infections. Data from this period were used to assess baseline antibiotic use.

**2) Preparation period (January 2026 to March 2026):**

This phase encompasses baseline data analysis, investigation of drivers of antibiotic use, development of the intervention package, staff training, and establishment of a multicenter data coordination mechanism.

**3) Intervention period (April 2026 to March 2027):**

The antimicrobial stewardship QI intervention is scheduled to be implemented simultaneously across all participating centers, with ongoing monitoring of relevant outcome and process indicators.

### Study setting and participants

2.3

This study is conducted concurrently across five NICUs in the Suqian region: Suqian First Hospital, Sihong Hospital, Sihong First Hospital, Shuyang Hospital of Traditional Chinese Medicine, and Siyang Hospital. These institutions serve as the primary referral centers for neonatal care within the region. The annual number of NICU discharges for each participating center in 2024 is presented in Table 1.

**Table 1 T1:** Characteristics of participating neonatal intensive care units in 2024.

Institution	Hospital level	Annual NICU admissions
Suqian First Hospital	Tertiary	862
Sihong Hospital	Tertiary	524
Sihong First Hospital	Secondary	395
Shuyang Hospital of Traditional Chinese Medicine	Tertiary	872
Siyang Hospital	Tertiary	484

#### Inclusion criteria

All neonates admitted to the NICUs of participating centers during the study period;Admission occurring within either the baseline or intervention period.

#### Exclusion criteria

Neonates with a confirmed diagnosis of severe infection prior to admission who had already received systemic antibiotic therapy;Neonates with missing key clinical data that precluded evaluation of the primary outcome measures.

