#### Primary outcomes

2.7.1

Antibiotic use rate: the proportion of neonates who received at least one course of systemic antibiotic therapy during the study period;AUR: defined as the number of antibiotic days per 1,000 patient-days.

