#### Balancing measures

2.7.2

Incidence of LOS: the number of sepsis cases diagnosed ≥72 h after birth based on positive blood cultures and/or compatible clinical syndrome, divided by the total number of NICU admissions during the same period and expressed as a percentage;All-cause in-hospital NICU mortality;Antibiotic re-initiation rate: re-initiation of systemic antibiotics within 3 days after antibiotic discontinuation.

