#### Data elements and sources

2.8.1

All participating centers collect data across three domains:

Baseline data: Data will be extracted from hospital electronic medical record systems and discharge summaries. Demographic and baseline clinical characteristics of enrolled neonates from both the pre-intervention (historical control) period and the intervention period will be collected, including sex, gestational age, birth weight, admission diagnoses, and comorbidities. In addition to patient-level data, center-level baseline characteristics will be collected for each participating NICU. These characteristics will include local microbiological resistance patterns (antibiograms) and baseline rates of hospital-acquired infections. These data will be used to describe inter-center differences that may influence empirical antibiotic prescribing practices.Process data: collected to calculate process measures, primarily using a standardized Antibiotic Use Case Registry Form. Key variables include a unique study identifier, date and indication for antibiotic initiation, completion of initiation assessment, documentation of the 48–72-h reassessment, and dates and results of blood cultures and other microbiological tests.Outcome data: collected to derive primary and balancing outcomes and extracted from electronic medical records and discharge summaries. These include daily antibiotic administration records (used to calculate antibiotic days), total length of NICU stay, dates and diagnostic basis of LOS, dates and causes of death, and records of antibiotic re-initiation following discontinuation.

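### The missing-data exclusion is applied to the infant rather than to the antibiotic outcomes, so as written it also drops recorded deaths and late-onset sepsis from the balancing measures

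*Protocol article*

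**What the plan says.** The study population is "All neonates admitted to the NICUs of participating centers during the study period", restricted to the baseline and intervention periods (section 2.3, Inclusion criteria). The second exclusion criterion then removes "Neonates with missing key clinical data that precluded evaluation of the primary outcome measures".

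The primary outcomes (2.7.1) are the antibiotic use rate, "the proportion of neonates who received at least one course of systemic antibiotic therapy during the study period", and the AUR, "defined as the number of antibiotic days per 1,000 patient-days". The balancing measures (2.7.2) are late-onset sepsis, with cases "divided by the total number of NICU admissions during the same period and expressed as a percentage"; "All-cause in-hospital NICU mortality"; and antibiotic re-initiation. None of the three is given an analysis population of its own. Section 2.9 makes the absence of an increase in any of them a condition for judging the programme successful.

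On data, section 2.8.1 lists deaths and sepsis diagnoses as items distinct from the day-by-day antibiotic records. The same section says that baseline characteristics of "enrolled neonates from both the pre-intervention (historical control) period and the intervention period will be collected". Section 2.2 places "establishment of a multicenter data coordination mechanism" in January to March 2026, after the baseline year has ended.

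**The concern.** An exclusion that depends on whether an effectiveness variable can be evaluated is a selection made after the fact. Here it acts on the infant, so incomplete antibiotic data also cost the study any safety event that infant had. A death can be fully documented when antibiotic days are not. Mortality and late-onset sepsis help decide success, so their counts should not depend on the completeness of a different variable.

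Two things follow. First, the sepsis denominator is worded as all admissions while the exclusion removes some admissions, so the population of that rate is unclear. Second, the design compares two periods. If the rule removed different shares of infants in each, and those infants differed in risk, part of the before-after contrast would come from selection rather than from the intervention.

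**Working it through.** **No figure to reproduce.** The article states no mortality, sepsis rate, missingness rate or power. The only usable input is Table 1 (2024 admissions): 862 + 524 + 395 + 872 + 484 = 3137 a year. Everything else below is an assumption.

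**Mortality.** Let p be true mortality, equal in both years; m the share excluded; RR the risk in excluded infants divided by overall risk.

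- Deaths removed = 3137 × m × RR × p
- Observed mortality = p × (1 − m × RR) / (1 − m)
- Spurious ratio = observed mortality in the intervention year / observed mortality at baseline

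With p = 1%, there are 3137 × 0.01 = 31.4 deaths a year.

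| Excluded, baseline / intervention | RR | Deaths removed | Observed mortality | Ratio |
|---|---|---|---|---|
| 2% / 2% | 3 | 1.9 / 1.9 | 0.959% / 0.959% | 1.00 |
| 5% / 1% | 1 | 1.6 / 0.3 | 1.000% / 1.000% | 1.00 |
| 2% / 0.5% | 3 | 1.9 / 0.5 | 0.959% / 0.990% | 1.03 |
| 2% / 0.5% | 5 | 3.1 / 0.8 | 0.918% / 0.980% | 1.07 |
| 5% / 1% | 3 | 4.7 / 0.9 | 0.895% / 0.980% | 1.10 |
| 5% / 1% | 5 | 7.8 / 1.6 | 0.789% / 0.960% | 1.22 |

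Example, last row: baseline 1% × (1 − 0.05 × 5) / 0.95 = 0.789%; intervention 1% × (1 − 0.01 × 5) / 0.99 = 0.960%; 0.960 / 0.789 = 1.22.

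The ratio does not depend on p, which cancels. It departs from 1.00 only when the shares differ and RR is not 1. If the shares are swapped, the ratios invert: 1/1.03 = 0.97 and 1/1.22 = 0.82, which would hide harm rather than suggest it. Even at equal shares, the first row shows recorded deaths being lost and both yearly rates understated.

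**Late-onset sepsis.** Set against the exclusion, the definition allows three readings:

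1. Cases and admissions both cover everyone admitted. The exclusion then does not touch this measure, contrary to its own wording.
2. Both cover eligible infants only. The denominator is then not all admissions, and the mortality formula above applies.
3. The exclusion acts on cases but not on admissions. The rate is then understated by the factor 1 − m × RR; at m = 2% and RR = 3 that is 1 − 0.06 = 0.94.

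The text does not choose between them.

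**Antibiotic use rate.** Missing records remain a question for this outcome under any rule. Suppose true use is 70% and 30% of excluded infants are treated (both assumed). With 5% excluded the observed rate is (70% − 0.05 × 30%) / 0.95 = 72.1%; with 1% it is (70% − 0.01 × 30%) / 0.99 = 70.4%. Counting missing infants as all treated and then as none treated gives bounds whose width equals the missing share, for example 5 percentage points at 5% missing.

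**The case against.** The strongest reply is that unequal exclusion is nowhere shown. A reader might infer that the rule removes more infants from 2025 than from the intervention year, because the baseline is historical, the coordination mechanism came later, and sections 2.8.2 and 2.8.3 describe monthly checks and quarterly audits. The documents do not establish this. No missingness rate is given for either year. Outcome data come from the same record types with no distinction by period. The registry form serves the process measures, and the historical-control wording sits under baseline characteristics. The checks and audits are neither said to cover 2025 records nor said to leave them out. This part of the reply stands: a difference between periods is a possibility only.

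A reader might also take the sepsis denominator as a proven mismatch. It is not. Only the third reading above produces one, and on the first the excluded infants' sepsis cases would still be counted. What stands is that the two sections do not fit together as printed.

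Finally, larger distortions can be constructed. If 10% of excluded infants die, with 5% against 1% excluded and 1% overall mortality, the ratio is 1.73 (0.526% against 0.909%). But 0.05 × 10% = 0.5%, so half of all baseline deaths would have to fall in the excluded 5%. Even the 1.22 case puts a quarter there (0.05 × 5). Nothing in the documents suggests such concentration, and 1.73 should not be used as the size of the problem.

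None of this answers the central point. The criterion is stated at infant level, it is triggered by antibiotic data, and mortality has no population that would escape it. It is a fixed eligibility rule, not a detail left to an analysis plan.

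**Conclusion.** The point holds in a limited form. Followed as written, the second exclusion criterion takes recorded deaths and late-onset sepsis out of measures that help decide success, for a reason unrelated to whether those events are known. That rests on the text alone. The sepsis denominator and the exclusion need to be reconciled.

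Bias in the before-after mortality comparison is conditional on unequal exclusion together with a different risk in excluded infants, and its direction is unknown. Under the assumptions shown, the spurious ratio is about 1.03 to 1.07 at 2% against 0.5% excluded and about 1.10 to 1.22 at 5% against 1%; it is 1.00 if either condition fails. At 1% mortality the 1.07 case is a difference of about two removed deaths (3.1 − 0.8 = 2.3). The article gives no size of increase that would count as a safety failure, so whether such a shift would change the conclusion cannot be said.

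Re-initiation is different in kind: it is itself derived from antibiotic records, so the argument applies to death and sepsis. The change is worth making because it is cheap and removes this selection from both.

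**What to change.** - Reword the second exclusion so that missing antibiotic data remove an infant from the antibiotic use rate and AUR only, with that infant's antibiotic days and patient-days both left out of AUR.
- Count deaths and late-onset sepsis over all otherwise eligible admissions, that is, after the first exclusion criterion. State that the sepsis numerator and denominator use this same population, and align section 2.7.2 with section 2.3.
- Report the number of infants with missing antibiotic data by period and center, so that any imbalance can be seen.
- Bound the antibiotic use rate by taking infants with missing data as all treated and then as none treated.

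The cost is a wording change, one table of counts and one simple sensitivity analysis. The small downside is the extra analysis and slightly wider bounds on the use rate where records are missing.

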### Sample size considerations

2.4

As this study is a QI initiative with monthly aggregated data as the primary unit of analysis, no formal sample size or power calculation based on individual-level hypotheses was performed. The study design includes 12 consecutive monthly data points before and after the intervention. Methodological literature indicates that ITS analyses typically require a minimum of 8–10 data points in both the pre- and post-intervention phases to establish stable baseline trends and detect meaningful changes over time (21, 22). Accordingly, the planned study design is considered sufficient to support statistical process control analyses and ITS regression modeling.

### Baseline assessment and root cause analysis

2.5

Before developing the intervention, we conducted a structured baseline assessment using 2025 data, informed by multidisciplinary discussions with NICU staff to identify drivers of high antibiotic use.

Through process mapping and multidisciplinary review, several key factors contributing to antibiotic overuse were identified, including:

Lack of standardized criteria for initiating antibiotic therapy;Risk-averse approach to early-onset sepsis (EOS) risk assessment;Absence of a systematic 48–72-h antibiotic reassessment process;Insufficient monitoring and feedback mechanisms related to antibiotic use.

These contributing factors were synthesized into a fishbone diagram (Figure 1) and served as the conceptual framework for the design of the antimicrobial stewardship QI intervention bundle.

**Figure 1 F1:**
[figure not shown]
Fishbone diagram illustrating key contributors to high antibiotic use in NICUs in the Suqian region. NICU, Neonatal Intensive Care Unit; EOS, early-onset sepsis; AUR, antibiotic utilization rate.

### Intervention

2.6

The antimicrobial stewardship intervention implemented in this study consists of a multicomponent clinical QI bundle, with the core objective of optimizing decision-making processes related to antibiotic initiation, reassessment, and discontinuation.

#### Module 1. establishment of a two-tier QI team structure

2.6.1

1) Regional steering committee

A regional steering committee was established and led by Suqian First Hospital. The committee comprises department directors from each participating center, directors of pharmacy services, infection control leads, and the principal investigators. The committee is responsible for developing unified standards, organizing training activities, coordinating data collection, and convening monthly review meetings.

2) Hospital-level core implementation teams

Each participating hospital established a core implementation team consisting of the NICU director (team lead), one to two senior attending neonatologists (designated liaisons), a clinical pharmacist, an infection control nurse, and a microbiology laboratory representative. These teams are responsible for local implementation of the intervention, data collection, routine audit, and feedback within their respective NICUs.

3) Multicenter coordination mechanism

All centers submit monthly data on process adherence to the regional steering committee and participate in cross-center discussions and feedback during monthly collaborative meetings. Each center designates fixed personnel responsible for overseeing antimicrobial stewardship processes. Cases deviating from the intervention protocol are explicitly flagged in monthly data reports and reviewed during collaborative meetings. Continuous monitoring of key process indicators promotes consistent implementation across centers.

The two-tier implementation structure is designed to minimize additional workload. Hospital-level core teams are composed of a small number of key personnel whose existing responsibilities already include clinical leadership, pharmacy, or infection control. Frontline clinicians are primarily engaged through the standardized clinical pathway at the point of care rather than through frequent additional meetings. Coordination, data aggregation, and feedback responsibilities are centralized within the hospital-level core team and the regional steering committee, whose monthly meetings are intended to consolidate previously unstructured, *ad hoc* communications into a more efficient feedback mechanism.

